### Participant recruitment

A total of 60 participants will be recruited at the beginning of a program cycle from approximately four consecutive program cycles, each of which is composed of 20 to 30 trainees. A new program cycle starts every four months. The first author will be responsible for the study approval procedure at the beginning of the course while providing information about the study to all trainees and inviting them to participate. The trainees’ decision to participate or not in the study will not affect their participation in the course in any way. The trainees who agree to take part in the study will sign an informed consent form that clarifies that participation in the study is on a voluntary basis and that anonymity and confidentiality are guaranteed as well as the right to withdraw at any time without this affecting their participation in the program. Participants who have a custodian will be required to present the custodian’s approval as well. This form will also include information about the data collection procedures, including data from the RRP personal file.

### Study design

This study will implement a randomized controlled trial (RCT) design to investigate a synchronous or non-synchronous movement-based group intervention, so that each participant will only engage in one intervention condition, alongside a phenomenological study with the participants of both groups. The RCT will compare the experimental group (synchronous movement) with a treated control group (non-synchronous movement) and will follow the recommendations of the Consolidate Standards of Reporting Trials (CONSORT) [51] and the recommendations of the Standards for Reporting Qualitative Research [52]. In addition, the SPIRIT guidelines [53] have been followed. Fig 1 outlines when each study component occurs. This design does not include a nontreated control group to meet the program’s requirement that all trainees should participate in all course activities including the movement-based group intervention. The study was registered with ClinicalTrials.gov (registration number: NCT05846308) afterthe enrolment of participants started due to the uncertainty about the clinical character of the target population and intervention. The authors confirm that all ongoing and related trials for this intervention are registered.

The condition groups will be matched according to the following control variables: (a) gender (male/female); since there is diagnostic gender bias with respect to ASD [54] (b) army related profession (image interpretation/GIS/data analytics/software programming/electro-optics/data annotation) (c) handedness (right-handed/left-handed); since there is a larger distribution of left-handedness in the ASD population compared to the general population [55] (d) need to belong level (NTBL) (high/low). To control for handedness and NTBL during the randomization process, the following questionnaires will be administered to the participants: (a) The Hebrew adaptation of the Edinburgh Handedness questionnaire [56], the most common method for measuring handedness in individuals with Autism [57]. (b) The Hebrew adaptation of the Need to Belong (NTB) Scale [59] which comprises ten items rated on a 5-point Likert scale ranging from “Strongly Disagree” (1) to “Strongly Agree” (5). This scale has acceptable interitem reliability (the Cronbach’s alpha generally exceeds .80) and has been positively correlated with extraversion, agreeableness, and neuroticism and with having an identity that is defined in terms of social attributes [58]. NTBL(high/low) will be calculated using a cut-off of the NTB measure, so that participants with the 50% highest NTB score will be assigned a high NTBL and the rest will be assigned a low NTBL. After inclusion in the study and assessment of the control variables, participants will be assigned by the first author to one of the intervention conditions on an individual basis according to a computer-generated randomization procedure. The allocation ratio of the intended numbers of participants in the comparison groups will be 1:1 so that the number of participants assigned to the synchronous intervention will be similar to the number of participants assigned to the non-synchronous intervention. To this end, we will first create subgroups containing participants with same gender, army-related profession, handedness and NTBL. For each subgroup, alternate assignments will be made in random order. The order of subgroup assignments will also be determined randomly. For the first subgroup, we will use a simple coin flip randomization procedure to determine the intervention type to start assigning to. An overview of the study design is shown in Fig 3.

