### Objectives

The aim of this study is to assess the effects of group interpersonal synchrony on the prosociality and work-related stress of young autistic adults in their work environment. The primary objective is to determine whether a synchronized group intervention will have an immediate and/or long-term positive effect on participants’ prosociality and work-related stress. The secondary objectives are to determine: (1) Whether a synchronized group intervention will have an immediate and/or long-term positive effect on participants’ social closeness and sense of belonging, (2) Whether this effect will be influenced by participants’ need to belong as reported before the intervention, (3) How participants perceive the intervention as affecting their prosociality and work-related stress, and (4) In what ways the participants’ perception will contribute to a better understanding of the intervention effect.

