### Sample size

A meta-analysis on prosocial consequences of interpersonal synchrony among neurotypical adults found a medium-sized effect of interpersonal synchrony on prosociality with regard to both attitudes and behavior towards individuals or groups involved in the same intervention [28]. Therefore, an effect defined as d = 0.25 may be expected [49]. An a-priori power analysis using the G*Power computer program [50] indicated that a total sample size of 40 participants would be needed to detect medium-sized effects defined as f = 0.25, with 80% power and alpha at .05, using a repeated measure, within-between interaction ANOVA with four groups and three measurements. We will recruit at least N = 60 participants (30 in each intervention group) to plan for possible dropouts.

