#### Quantitative data analysis

The data obtained as study variables will be coded, processed and analyzed at the end of the collection process. IBM SPSS Statistics Version 27 will be used for statistical analysis. To control the family-wise error rate when performing multiple hypothesis tests, Bonferroni Step-Down (Holm) procedure will be applied. Participants must attend at least 4 sessions to be included in the analyses. To describe the sample, descriptive statistics will be calculated followed by univariate and bivariate statistical analyses. The first step will be to assess whether the data follows a normal distribution for each of the variables which will guide the choice of parametric or non-parametric tests. To answer the primary study objective and the first secondary study objective, the effects of the intervention over time (at the end of the intervention and after 17 weeks) will be examined using a two-way mixed model ANOVA. To explore the second secondary study objective, the influence of the need to belong on the effect of the intervention over time (at the end of the intervention and after 17 weeks) will be examined using a three-way mixed model ANOVA.

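### The moderation test evidently uses need to belong as a high/low split rather than as a score, which costs about a third of the information for secondary objective 2

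*Protocol article*

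**What the plan says.** - **Objective.** The Objectives section of the Protocol article lists as secondary objective 2: "Whether this effect will be influenced by participants’ need to belong as reported before the intervention".
- **Scale.** Under Study design, the NTB Scale is described as one "which comprises ten items rated on a 5-point Likert scale".
- **Split.** The same section sets the high/low need-to-belong level (NTBL) relative to the sample: "participants with the 50% highest NTB score will be assigned a high NTBL and the rest will be assigned a low NTBL". No fixed score is given. The stated purpose is allocation: "To control for handedness and NTBL during the randomization process, the following questionnaires will be administered to the participants".
- **Moderation test.** Under Quantitative data analysis, the influence of need to belong on the effect over time "will be examined using a three-way mixed model ANOVA". The text does not say whether the score or the level enters.
- **Sample size.** The Sample size section obtains 40 participants from a "within-between interaction ANOVA with four groups and three measurements", although the trial has two arms. It then plans to recruit at least 60.
- **Timing.** Participants come from "approximately four consecutive program cycles, each of which is composed of 20 to 30 trainees", and NTBL must be known before allocation: "After inclusion in the study and assessment of the control variables, participants will be assigned by the first author to one of the intervention conditions".

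**The concern.** An ANOVA with condition, time and need to belong as its three factors needs a categorical version of need to belong, and NTBL is the only one defined. If it is used, everyone above the cut is treated as alike and everyone below it as alike. The hypothesis in the section on the moderating factor is worded as a matter of degree, and the questionnaire yields a graded score.

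A moderation test in 60 people is weak to begin with. Dichotomising the moderator weakens it further, so a real moderating effect is more likely to be missed and a null result harder to interpret.

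**Working it through.** **1. The plan's own figure.** Inputs from the Sample size section: f = 0.25, power 80%, alpha .05, k = 4 groups, m = 3 measurements. Assumed, because not stated: the G*Power defaults, correlation ρ = 0.5 and sphericity ε = 1.

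- λ = f²·N·m/(1 − ρ) = 0.0625 × 40 × 3 / 0.5 = 15
- df1 = (k − 1)(m − 1) = 6; df2 = (N − k)(m − 1) = 36 × 2 = 72
- Power = 0.805 at N = 40, so the stated 40 is reproduced.

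With k = 2 and the same defaults, 28 participants would be enough (power 0.812). The calculation therefore did use four groups. Two arms × two NTBL levels is the natural source of four groups in a two-arm trial with this moderation objective.

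**2. Information kept by a median split.** For a normal score, the squared correlation between the score and its median-split indicator is 2/π = 0.637. With linear moderation this is the fraction of information retained.

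- Loss: 1 − 0.637 = 36.3%
- 60 participants: 60 × 0.637 = 38.2
- 40 participants: 40 × 0.637 = 25.5
- Sample size multiplier to recover the loss: 1/0.637 = 1.57

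**3. Power.** Take a test with exactly 80% power on the continuous score. Its noncentrality is 1.960 + 0.842 = 2.802. After the split it is 2.802 × √0.637 = 2.236, and power is Φ(2.236 − 1.960) = 0.608. The noncentral t gives 0.609 at both N = 40 and N = 60.

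A simulation gives a similar picture. It used N = 60, arm coded ±0.5, normal NTB, a single change score with residual SD 1, and a linear arm × NTB effect b per NTB SD. The values of b are illustrative and do not come from the documents.

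| b | Continuous score | Pooled median split | Split within four cycles of 15 |
|---|---|---|---|
| 0.8 | 82% | 64% | 61% |
| 0.5 | 47% | 31% | 29% |

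**4. Cycle-by-cycle labels.** For allocation, the 50% point can only be set on the participants then available, that is, within a cycle. With no true difference between cycles, simulation gives:

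| Cycles × participants | Labelled differently from a pooled split | Information loss |
|---|---|---|
| 4 × 15 = 60 | about 9% | 41% |
| 3 × 20 = 60 | 7% | 40% |
| 4 × 24 = 96 | 7% | 39% |

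The expected gap between the highest and lowest of four cycle cut-offs is 0.65 NTB SD at 15 per cycle and 0.51 at 24. Against the 36% loss from a pooled split, the added harm is small: 2–3 points of power in the table in step 3.

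**The case against.** **The article never says the split enters the ANOVA.** Study design ties NTBL to randomisation, and the objective and the analysis section both speak simply of need to belong. Coding of a moderator is often left to an analysis plan, which is not at hand here. This stands as a caveat: the use of NTBL in the analysis is inferred. But the article does fix the type of test, and its sample size uses four groups, so the inference is strong.

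**The moving cut-off.** A reader might infer that high need to belong will mean a different score in each cycle when moderation is tested. The documents do not support that. Cycle-wise cutting follows for allocation only, where a relative split is unobjectionable. Nothing says whether the label is carried forward or re-cut on the pooled sample. If it is re-cut, the point disappears from the analysis and the 36% loss remains. If it is carried forward, the extra loss is minor.

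**Linearity.** The article gives no functional form. If the moderator were a true threshold at the median, the ranking would reverse: in a simulation with b = 0.8, the continuous test had 65% power and the pooled split 76% (64% if cut within cycles). This stands, and the case for the score therefore depends on a roughly linear relation.

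**Coherence with the design.** Analysing the factor used for balancing is legitimate. It is less efficient under linearity, not invalid.

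**Conclusion.** The plan evidently dichotomises NTB for the moderation test. Under a roughly normal score and linear moderation, this gives up about 36% of the information: 60 participants count as about 38, and about 80% power on the score becomes about 61–64% on the split. A skewed or heavily tied score would change these figures, and a threshold at the median would favour the split.

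Labels that differ by cycle are a side point, affecting 7–9% of participants and 2–3 points of power, and only if the allocation label is carried into the analysis.

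A reader might take this as a flaw in the trial's main result. It is not: it concerns secondary objective 2 only, and neither the primary comparison nor the use of NTBL in allocation is affected. It is a cheap and worthwhile improvement.

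**What to change.** - Keep NTBL for balancing the allocation only.
- State that moderation is tested as arm × time × continuous, mean-centred NTB score in the mixed model.
- Report the arm effect at chosen NTB percentiles, for example the 25th and 75th, and check linearity by plot.
- If a high/low display is wanted, give it as a secondary presentation with one cut-off from the pooled sample.

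Cost: small, and no new data are needed because the score is already collected. A linear form is assumed. The Sample size section rests on four groups, so its basis must be restated to match the new analysis. Under Study status, three cycles are complete and a fourth is in progress, so this would be a mid-trial change of analysis. It must be documented and dated before outcome data are examined.

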**Fig 3 pone.0307956.g003:**
[figure not shown]
Flow of participants through the study: Illustration of the study design. Note: EHQ, Edinburgh Handedness Questionnaire; NTB, Need to Belong Scale; IOS, Inclusion of Other in Self Scale; FCI, Friendship Closeness Inventory; GSB, General Sense of Belonging Scale; IS, Irritation Scale; CT, Collection Task; PGG, Public Goods Game.

### Procedure

The interventions will be conducted by the first author, who is a professional Dance Movement therapist, as part of the RRP course, once a week for the duration of the 10 weeks of each program cycle. A graduate student of the RRP will take part as a co-instructor for modelling and assistance. Each intervention group will have between 10 and 14 participants. Since autistic participants may feel anxious without a predictable structure, a structured physical training protocol will be used for each condition. The protocols were designed by the first author with the help of a professional physical trainer and after consulting with dance movement therapists who have research experience in the area of synchrony interventions in ASD. Each protocol is composed of 10 physical training sessions, each lasting 60 minutes. The protocols differ in terms of using synchronous activity vs. non-synchronous activity. They do not differ in terms of physical exercise type or duration to control for the effect of exercise type and duration on the dependent variables. Some exercises include the use of a training mattress, an elastic band or a sponge ball. To allow for some flexibility in terms of spontaneous synchrony, each session includes a social engagement segment either as a warm-up or as a social game. A Tabata Timer [59] will be used to break the workout into clearly defined intervals during the main training segment. A metronome beat (every second) will be used to help the participants do the exercises at the right pace.

### Synchronous condition

The instructors and the participants will form a circle facing each other while doing the physical exercises as shown in Fig 4. To facilitate interpersonal synchrony, the participants will be instructed to do the same physical exercises (spatial synchrony) together at the same pace (rhythmic synchrony). The participants will not be instructed to use the same amount of effort, to accommodate a range of strengths and intensities.

**Fig 4 pone.0307956.g004:**
[figure not shown]
Synchronized group intervention.

### Non-synchronous condition

The participants will do the same physical exercises as the participants in the synchronous group but in the form of circuit training with seven stations. The circuit training will require the participants to do a different physical exercise at a different pace at each station. A detailed description of the exercises will be provided for each station. The instructors will demonstrate all the exercises before the beginning of training. The participants will be instructed to do the exercise for a set period of time, the same duration used in the synchronous group. The circuit training stations will be in the form of a circle, as shown in Fig 5, but will be set up so that the participants do not to face each other when doing the exercises to prevent spontaneous synchronization. Depending on group size, the participants will work either as dyads or as single trainees in each station. In the dyad form one participant will do the exercise while the partner is resting and vice-versa. In the single form each participant will exercise as though a partner were present. The participants will be instructed to change partners each week so that each participant will have the opportunity to experience both the single and dyadic forms, with different partners.

**Fig 5 pone.0307956.g005:**
[figure not shown]
Non-synchronized group intervention.

### Intervention protocol

Each session will consist of four parts as listed in Table 1.

**Table 1 pone.0307956.t001:** Intervention protocol.

Part	Sub part	Synchronous condition	Non-synchronous condition
**Warm-up** (10 minutes)	Body joints warm-up: neck, shoulder, pelvis, hip and ankle	Rotating the joints four times on each side of the body together at the same pace.	Rotating the joints four times on each side of the body, at each participant’s own pace.
	Cardio warm-up: running, jumping skipping	Moving together in a circle while instructed to keep the same pace.	Moving in a form of relay race, at each participant’s own pace.
**Social Game** (10 minutes)	Each session will contain a different movement game such as catch and “numbers in a circle” (outdoor training game). The social flexibility of the game will be gradually increased during the intervention period thus allowing for spontaneous synchrony.		
		For example: in the “catch” game the participants will have to pass a ball to each other 21 times simultaneously, thus depending on each other to successfully complete the game.	For example: in the “catch” game the participants will have to bounce the ball against a wall 21 times and catch it, thus depending on their own performance to successfully complete the game.
**Main training** (30 minutes)	Each session will contain two sets, each consisting of seven fixed exercises with a resting period of 10–15 seconds between each. Each exercise combines strength only (20–30 sec) or strength (20–30 sec) and cardio (15 sec). There will be a resting period of 3 minutes between each set of exercises. Each exercise will be performed at one of three different paces: *Slow—*one movement cycle per 2 seconds, *Medium—*one movement cycle per 1 second and *Fast*—two movement cycles per 1 second, to allow for the non-synchronous group to do the same exercises as the synchronous group in non-synchronized way (both spatial and rhythmic).		
	Legs and upper body set (e.g., squats, heel raising, arm rotations etc.)	Performing the same physical exercises together at the same pace in a circle facing each other.	Performing different physical exercises at a different pace in a circuit training setup.
	Back and abdomen set (e.g., pushups, planks, crunches etc.)		
**Cool-down** (10 minutes)	Muscle stretching: arms, hands, thighs, legs and feet	Stretching eight counts on each side of the body together at the same pace.	Stretching eight counts on each side of the body, at each participant’s own pace.
	Relaxing	Performing eight breathing cycles together at the same pace.	Performing eight breathing cycles, at participant’s own pace.

### Quantitative data collection: Background and control variables

Background and control data will be collected for each participant from the RRP personal file which contains demographic and medical information obtained by the program staff using dedicated questionnaires. The questionnaires are handed out routinely to all RRP trainees during the program selection process, a few months before admission to the program. These cover information such as demographic data (e.g. age, gender, country of birth, residential area, number of siblings and birth order), medical data (e.g. diagnosis, age at diagnosis, comorbidities, use of psychiatric medication and HMO disability bracket) and physiological data (e.g. body weight and height).

### Quantitative data collection: Outcome variables

Quantitative data on the following outcome variables (as listed in Table 2) will be collected for each participant using validated questionnaires and behavioral tasks at three points of time: before the first intervention session, after the last intervention session (pre-post) and 17 weeks after the end of the intervention period (follow-up). The data collection procedure will be administered by the first author in a group session, corresponding to the same group as the intervention group, in a classroom at RRP facilities. This procedure will be composed of two parts: (a) A group behavioral task which will be recorded using one video camera. (b) Questionnaire administration via online software (Qualtrics).

**Table 2 pone.0307956.t002:** Study outcomes.

Outcomes

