#### Social closeness

Social closeness will be measured using the Inclusion of Other in Self Scale (IOS) [60, 61]. This scale is made up of seven Venn diagram-like pictures where one circle represents the participant and the other circle represents the entire intervention group. The diagrams, ranging from no overlap to near complete overlap, measure close relationships between self and the group by capturing aspects of both feeling close and behaving close. The scale has high reliability for the friendship subgroup sample (Cronbach’s alpha .92) and a high test-retest correlation (r = .86 (n = 31)). Significant correlations between the IOS and measures of closeness that are primarily verbal and multi-item were found (60).

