
*2*. *Public goods game*. Participants will be told they will be given 30 NIS and that they can donate some or all of it to a group investment, as described in [68]. The money in the group investment will then be doubled and divided equally among all members of the group. The money earned in this game will be compensation for participating in the study. In contrast to the collection task, participants’ contribution will be confidential to avoid group pressure. Cooperation on this task will be operationalized by the amount of money each participant decides to donate to the group investment.

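### Participants are treated and assessed in session groups but analysed as independent, so the condition-by-time test exceeds its nominal 5% if the groups diverge after baseline

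*Protocol article*

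**What the plan says.** - **Allocation.** The Study design section assigns individuals 1:1, after sorting them by gender, profession, handedness and need-to-belong level.
- **Delivery.** Treatment is given weekly for 10 weeks in groups: "Each intervention group will have between 10 and 14 participants" (Procedure).
- **Measurement.** At all three time points the data collection is "administered by the first author in a group session, corresponding to the same group as the intervention group" (Quantitative data collection: Outcome variables).
- **Group as object of the outcome.** In the social closeness scale "the other circle represents the entire intervention group". The belonging scale and the friendship inventory are reworded to refer to members of the training group.
- **Analysis.** The primary objective and the first secondary objective "will be examined using a two-way mixed model ANOVA". A three-way version adds need to belong, and Holm is the multiplicity step (Quantitative data analysis). Session group and program cycle do not appear.
- **Sample size.** The calculation takes a 5% alpha, a power of 80% and a medium effect of f = 0.25, and was run "using a repeated measure, within-between interaction ANOVA with four groups and three measurements". It gives 40. The increase to at least 60 is attributed to dropout only.

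**The concern.** Individual randomisation makes the groups comparable at the start. It does not keep members of a group independent once they share ten sessions, the same group-mates and the same assessment session. The article's own rationale is that moving together bonds a group, so some groups may bond more than others for reasons unrelated to synchrony.

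A between-within ANOVA judges the condition-by-time effect against variation between participants. Group-specific change does not average out over 30 participants per condition. It averages out only over the few groups in that condition. With about four groups per condition, one unusually cohesive or unhappy group can look like a synchrony effect. The standard error is then too small and the confidence interval too narrow.

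**Working it through.** **1. The plan's own figure.** For the within-between interaction, λ = f²·N·m/(1−ρ), df1 = (k−1)(m−1), df2 = (N−k)(m−1). The article gives f = 0.25, k = 4 groups and m = 3 measurements. It does not state ρ or sphericity, so I assume ρ = 0.5 and sphericity.
- N = 40: λ = 0.0625 × 40 × 3 / 0.5 = 15, df 6 and 72, power 0.805.
- N = 36: power 0.749.

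So 40 reproduces, with every participant counted as independent in df2. The four groups match neither the two conditions nor the number of session groups, so they are not an allowance for clustering.

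**2. Layout (inferred).** Participant recruitment gives about four cycles of 20 to 30 trainees and 60 participants. One group per condition per cycle (assumed) gives 4 × 2 = 8 groups, and 60/8 = 7.5 study participants per group. The stated 10 to 14 per group would give 80 to 112 over eight groups. The figures fit if trainees outside the study share the sessions, since Study design says all trainees take part in course activities: 20 to 30 split in two is 10 to 15.

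**3. Design effect.** DE = 1 + (m−1)·ICC, where m is now the group size of 7.5. Actual two-sided error of a 5% contrast = 2·[1 − Φ(1.96/√DE)]. The ICC is that of the change from baseline. Its range is assumed.

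| ICC | DE | SE too small by factor | Actual error | 60/DE | 40 × DE, rounded up |
|---|---|---|---|---|---|
| 0.01 | 1.065 | 1.03 | 5.8% | 56.3 | 43 |
| 0.05 | 1.325 | 1.15 | 8.9% | 45.3 | 53 |
| 0.10 | 1.650 | 1.28 | 12.7% | 36.4 | 66 |
| 0.20 | 2.300 | 1.52 | 19.6% | 26.1 | 92 |

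**4. Simulation of the planned test.** The condition-by-time F test (2 df) was simulated with no treatment effect, eight groups of 7 or 8, ρ = 0.5, and a group effect that arises after baseline and persists to follow-up.
- ICC 0: about 5%
- ICC 0.01: 5-6%
- ICC 0.05: about 9%
- ICC 0.10: 12-14%
- ICC 0.20: 16-22%

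If half of the group variance is instead specific to each occasion, the same layout gives about 10-11%, 15-17% and 27-30% at ICC 0.05, 0.10 and 0.20. The list above is therefore not an upper limit for those ICCs. A t test on group-mean changes (8 − 2 = 6 df) held about 5% throughout.

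**5. What cancels.** A group effect of equal size at all three time points drops out of the condition-by-time contrast, and the test stays at 5%. Only divergence after baseline matters.

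**6. Cycle.** Both conditions run in every cycle, so change shared by a cycle balances between conditions. When such cycle variance was added, a group-level test that ignored cycle became conservative, at roughly 2% to 3.5%. Pairing group means by cycle (4 − 1 = 3 df) held about 5%.

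**The case against.** **The size is assumed.** This stands. No ICC is given, and at 0.01 the excess is under one percentage point in the inferred layout. A reader might infer that the error rate certainly exceeds 5%. The article supports that only if groups change differently after baseline.

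**Not every outcome is shown to be affected.** This also stands. A reader might infer that all primary and secondary tests are inflated.
- *Public goods game.* Pooled money is "doubled and divided equally among all members of the group", but the outcome is each person's confidential donation. A shared payoff does not by itself correlate donations. Shared expectations about the same group-mates make correlation plausible and no more.
- *Collection task.* The outcome is individual step rate. With a fixed pool of 100 washers, one member's effort can replace another's, so the correlation could be negative.
- *Work-related stress.* The items refer to the course, which both conditions attend. Shared course stress is a cycle effect and balances. A session-group component is plausible but not demonstrated.

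**Larger error rates do not fit the trial.** Eight groups of 12 would give about 30% at ICC 0.20, but 8 × 12 = 96 participants against a planned 60.

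**Power may survive.** Partly right. With the two randomised conditions, k = 2 needs only N = 28 (81% power), and 28 × 1.65 = 46.2 at ICC 0.10 is below 60, before dropout and the loss of group-level degrees of freedom. Extra participants do not repair the false-positive rate.

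**Other safeguards.** Holm divides alpha among tests but takes each p-value as valid. The term mixed model ANOVA could be read as a model with random group effects, but the Sample size section describes the ordinary within-between ANOVA. A fuller analysis plan could add a group term, but the article already names the test and computes the sample size to match it.

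**Conclusion.** The concern holds in conditional form. The article fixes an analysis and a sample size that treat participants as independent, although they are treated and assessed in the same session groups. If groups diverge after baseline, the planned condition-by-time test is anti-conservative. In the inferred layout the excess runs from negligible at ICC 0.01 to two or three times the nominal level at ICC 0.10.

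This rests on three assumptions: the ICC range, one group per condition per cycle over four cycles, and a within-person correlation of 0.5. The direction is best supported for social closeness, adapted belonging and friendship closeness, which are secondary outcomes. Among the primary outcomes it is plausible for stress and donations and open for step rate.

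The three-way ANOVA has the same error structure, but the figures above are for the two-way test. Need to belong varies within groups, so the three-way interaction itself is less exposed to a shared group effect.

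The arithmetic behind 40 is not at fault. Its independence assumption is.

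**What to change.** 1. Replace the two-way and three-way ANOVAs with a linear mixed model (SPSS MIXED) that has participant effects, program cycle as a block whose effect may differ over time, and a random effect for session group at the two post-baseline occasions.
2. Use Satterthwaite degrees of freedom, and keep the group term even if its variance is estimated near zero.
3. State in advance whether one group effect is shared by post-intervention and follow-up or each has its own, because step 4 of the working shows that this matters.
4. As a simple check, compare group-mean changes between conditions, paired by cycle, separately at each occasion. The simulations covered group-level tests of this kind and not the mixed model itself, so this check is worth reporting beside it.
5. Report the ICC for each outcome.
6. Restate power in the Sample size section with 1 + (m−1)·ICC over a range such as 0.01 to 0.10, and state the number of session groups and of study participants in each. Enrolment need not change.

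**Cost.** A change of analysis wording and a few lines of syntax, using group and cycle membership that the trial already has. The article says analysis follows the end of data collection and that the fourth cycle is still running, so the change can be recorded before outcomes are analysed. The price is wider intervals and few group-level degrees of freedom, about 3 (paired by cycle) to 6 (unpaired).
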